#### Secondary outcomes

2.10.2

·Changes in self-management behaviors: Dietary habits, physical exercise, medication adherence, smoking management, alcohol management, sleep management, quality of life, and activities of daily living.·Social cognition and psychology: NSLBP health literacy, self-efficacy, depression, anxiety, stress, and social support.·Control of physiological indicators: blood pressure, height, weight.·Additionally, recruitment rates, dropout rates, and reasons for dropout will be collected. To ensure data homogeneity, demographic characteristics and study outcomes of dropouts and participants with adversarial attitudes toward the trial will be compared during data analysis.

### Variables measurement

2.11

Sociodemographic variables will be collected at baseline. Physical examinations and questionnaire surveys will be conducted at baseline, at discharge, at the end of the intervention, and at 3, 6, and 9 months post-intervention (Table 1).

**Table 1 tab1:** The schedule of enrolment, interventions, and assessments.

Study period	Recruitment	Intervention		Follow-up		
Timepoint	0	Discharge	3 Months	3 Months	6 Months	9 Months
Eligibility screen	√					
Informed consent	√					
Allocation	√					
Sociodemographic variables	√					
VAS	√	√	√	√	√	√
RMDQ	√	√	√	√	√	√
OPFEAS	√	√	√	√	√	√
PHQ4	√	√	√	√	√	√
PSSS-SF	√	√	√	√	√	√
NGSES-SF	√	√	√	√	√	√
EQ-5D-5L	√		√	√	√	√
IPAQ-SF	√		√	√	√	√
Smoking	√		√	√	√	√
Alcohol consumption	√		√	√	√	√
B-PSQI	√		√	√	√	√
SREBQ	√		√	√	√	√
FCS-SF	√					
eHEALS	√					

VAS, visual analog scale; RMDQ, The Roland-Morris Disability Questionnaire; OPFEAS, The Orthopedic Patient Functional Exercise Adherence Scale; PHQ-4, the abbreviated Patient Health Questionnaire-4; PSSS-SF, The Perceived Social Support Scale; NGSES-SF, The New General Self-Efficacy Scale-Short Form; EQ-5D-5L, EuroQol-5 Dimensions 5 Levels; IPAQ-SF, The International Physical Activity Questionnaire Short Form; B-PSQI, The new Brief Version of the Pittsburgh Sleep Quality Index-Short Form; FCS-SF, The Family Communication Scale-Short Form; SREBQ, The Self-Regulation of Eating Behavior Questionnaire; eHEALS, The eHealth Literacy Scale.

Sociodemographic variables to be collected include gender, age, marital status, location, average household size, educational level, and occupation, along with clinical information such as the duration of NSLBP and detailed medical history. Anthropometric variables: Each participant’s height, weight, waist circumference, and blood pressure will be measured twice using certified instruments. Height and weight will be measured using fully calibrated, certified electronic devices. Body Mass Index will be calculated by dividing weight (in kilograms) by height (in meters) squared. Waist circumference will be measured at the level of the navel using a tape measure. As for blood pressure, systolic and diastolic pressures will be measured using a validated automatic sphygmomanometer.

### Questionnaires

2.12

·The Visual Analog Scale (VAS) for pain is one of the most commonly used standards for assessing pain. It employs a 10 cm line to represent the continuum of pain severity, marked with numerals from 0 to 10 to indicate varying degrees of pain. A score of 0 signifies “no pain” while 10 denotes “unbearable pain.” Participants are asked to mark a point on the line that corresponds to their subjective experience of pain, thereby quantifying the intensity of their pain (38).·The Roland-Morris Disability Questionnaire (RMDQ) is a scale used to assess functional disability in patients with lower back pain (39). It consists of 24 items, each related to limitations in daily activities associated with lower back pain. Patients respond with “yes” or “no” to each item based on their condition to assess the impact of lower back pain on their daily activities. The scoring system is as follows: if a patient indicates that they are unable to perform an activity due to back pain, the item is scored as “yes” with 1 point; if the patient can perform the activity, the item is scored as “no” with 0 points. The total score is the sum of all item scores, ranging from 0 (no disability) to 24 (maximum disability). The scale has demonstrated high internal consistency, with Cronbach’s *α* values ranging from 0.84 to 0.96 (39).·The Orthopedic Patient Functional Exercise Adherence Scale (OPFEAS) is designed to evaluate the adherence of orthopedic patients to functional exercises during treatment and rehabilitation (40). This scale includes 3 dimensions and 15 items that cover exercise adherence related to physical, psychological, and proactive learning aspects. It uses a 5-point Likert scale, where 1 indicates “not at all able” and 5 indicates “completely able,” with higher scores reflecting higher adherence to functional exercises. It has demonstrated excellent internal consistency, with a Cronbach’s *α* of 0.930.·Depression and anxiety will be assessed using the abbreviated Patient Health Questionnaire-4 (PHQ-4), a brief self-report tool designed to evaluate symptoms of depression and anxiety over the past 2 weeks (41). The scale consists of four items, with the first two items related to depression and the last two related to anxiety. Each item is scored on a 4-point scale, with scoring options of “Not at all,” “Several days,” “More than half the days,” and “Nearly every day,” corresponding to scores of 0, 1, 2, and 3, respectively. The total score ranges from 0 to 12 points, with a Cronbach’s alpha of 0.833 (42).·The Chinese version of Perceived Social Support Scale PSSS-SF is designed to assess an individual’s perception of social support (43). The scale comprises three items across three dimensions: family support (item 1), friend support (item 2), and other support (item 3). It utilizes a 7-point Likert scale for scoring, ranging from 1 (strongly disagree) to 7 (strongly agree), with total scores ranging from 3 to 21. Higher scores indicate a higher level of perceived social support, and the scale has demonstrated good internal consistency, with a Cronbach’s *α* of 0.84 (44).·The Chinese version of New General Self-Efficacy Scale-Short Form (NGSES-SF) is used to evaluate an individual’s confidence and belief in their ability to successfully complete tasks or handle challenges (45). This scale includes three items across three dimensions: level or degree of self-efficacy (item 1), intensity (item 2), and generality (item 3), using a 5-point Likert scale for scoring, ranging from 1 (strongly disagree) to 5 (strongly agree), with total scores ranging from 3 to 15. Higher scores reflect a higher level of individual self-efficacy, and the scale has demonstrated good internal consistency, with a Cronbach’s *α* of 0.876 (45).·The Chinese version of Quality of life will be assessed using the EQ-5D-5L (EuroQol-5 Dimensions 5 Levels). The EQ-5D-5L encompasses five dimensions: Mobility, Self-care, Usual activities, Pain/Discomfort, and Anxiety/Depression. Individuals select the appropriate level for each dimension based on their personal health status, forming a five-dimensional profile ranging from no problems to extreme problems (46). In addition to the descriptive system, the EQ-5D includes a VAS, allowing individuals to subjectively rate their current health status on a scale from 0 to 100. This score provides a continuous variable for measuring an individual’s overall quality of life. In seven studies involving cancer patients, the EQ-5D demonstrated high validity and reliability, with Cronbach’s alpha values ranging from 0.72 to 0.90 (47–53).·The Chinese version of International Physical Activity Questionnaire Short Form (IPAQ-SF) consists of seven items designed to assess physical activity among adults aged 15 to 69 over the past 7 days, including vigorous, moderate, and walking activities (54). Participants are required to report the frequency and duration of each type of activity, as well as sedentary time during weekdays. Scoring is conducted by converting activity duration into metabolic equivalent of task (MET) minutes per week, with different activities assigned varying MET values, thereby quantifying an individual’s total physical activity level. This instrument is extensively utilized in public health research to evaluate population-level physical activity levels and their associated health impacts. It has demonstrated acceptable reliability, with an intraclass correlation coefficient (ICC) of 0.79 and a coefficient of variation (CV) of 26% (55).·Smoking behavior is measured using a self-constructed questionnaire consisting of four multiple-choice questions that assess whether an individual smokes, the number of years since quitting, the number of cigarettes smoked per day, and the duration since starting smoking (56). Respondents will be asked, “Do you have a habit of smoking?” The answer options are: (1) Yes, I smoke regular cigarettes; (2) Yes, I vape; (3) Yes, I use both; (4) I used to smoke (but have quit); (5) No. Based on the responses, smoking status is categorized into two groups: (1) Smoker: currently smokes; (2) Non-smoker: never smoked or has quit smoking.·Alcohol consumption is measured using a self-constructed questionnaire with seven multiple-choice questions that assess whether an individual drinks alcohol, age at the start of drinking, age at cessation of drinking, type of alcohol consumed, amount of alcohol consumed per day, amount of alcohol consumed per day before quitting, and anxiety about quitting alcohol. Respondents will be asked, “Do you currently or have you in the past consumed alcohol?” The answer options are: (1) I never drink; (2) I always drink; (3) I used to drink but now I do not; (4) I did not drink in the past but I do now.·The Chinese version of new Brief Version of the Pittsburgh Sleep Quality Index-Short Form (B-PSQI) is a condensed version of the Pittsburgh Sleep Quality Index, used to measure an individual’s sleep quality (57). The scale consists of 6 items across 5 dimensions, specifically measuring sleep efficiency (items 1 and 2), sleep onset time (item 3), sleep duration (item 4), sleep disturbances (item 5), and overall sleep quality (item 6). Bedtime and wake-up time are used to calculate sleep efficiency, with a total score ranging from 0 to 15; higher scores indicate poorer sleep quality. The scale has demonstrated acceptable internal consistency, with a Cronbach’s *α* of 0.79 (57).·The Chinese version of Family Communication Scale-Short Form (FCS-SF) is used to measure communication abilities within the family system (58). This scale consists of 4 items across a single dimension and utilizes a 5-point Likert scale, with scoring options ranging from 1 (strongly disagree) to 5 (strongly agree). Total scores range from 5 to 20, where higher scores indicate a higher level of family communication. The scale has demonstrated excellent internal consistency, with a Cronbach’s *α* of 0.91 (58).·The Chinese version of Self-Regulation of Eating Behavior Questionnaire (SREBQ) is used to assess an individual’s ability to regulate their eating behaviors (59). This scale consists of 5 items across a single dimension, using a 5-point Likert scale with scores ranging from 1 (never) to 5 (always). Total scores range from 5 to 25, with higher scores indicating greater ability in regulating one’s dietary habits. The scale has demonstrated acceptable internal consistency, with a Cronbach’s α of 0.75 (59).·The Chinese version of eHealth Literacy Scale (eHEALS) is designed to comprehensively evaluate an individual’s knowledge, ease of use, and perceived skills in searching, evaluating, and applying electronic health information to solving real health problems (60). This scale includes 5 items across a single dimension, utilizing a 5-point Likert scale, with scoring options ranging from 1 (strongly disagree) to 5 (strongly agree). Total scores range from 5 to 25, with higher scores indicating a higher level of personal eHealth literacy. It has demonstrated excellent internal consistency, with a Cronbach’s *α* of 0.913 (61).

### Statistical analysis

2.13

In this study, quantitative data will be collected through questionnaires and stored in Microsoft Excel format. Data analysis will follow the intention-to-treat principle. For continuous variables, results will be presented as mean ± standard deviation or as median with interquartile range (P25, P75), depending on the normality of the distribution, which will be assessed using the Kolmogorov–Smirnov test. Appropriate statistical methods, such as Student’s t-test, one-way ANOVA, or non-parametric tests, will be used for group comparisons. Categorical variables will be expressed as counts and percentages (n, %) and analyzed using the chi-square test.

To explore the relationships between behavioral patterns and mobile health application use, linear regression, logistic regression, and structural equation modeling will be applied to cross-sectional data. For longitudinal analyses, generalized linear mixed models will be used to assess the impact of AI-HEALS interventions on behavior change and NSLBP management over time. Subgroup analyses will be conducted based on patients’ levels of family communication and eHealth literacy to refine and contextualize the findings.

Missing data will be addressed using multiple imputation by chained equations (MICE), with 50 iterations to ensure convergence. Predictive mean matching (PMM) with five nearest neighbors will be employed, generating 20 imputed datasets. All statistical tests will be two-sided, with a significance level set at 0.05. Data will be analyzed using IBM SPSS Statistics 24.0 (SPSS Inc., Chicago, IL, United States), Stata 14.0 (StataCorp, College Station, TX, United States), and Mplus 7.4 (Muthén & Muthén, Los Angeles, CA, United States).

Upon completion of the intervention and at 3, 6, and 9 months post-intervention, structured interviews will be conducted with participants to gather feedback. The structured interview guide will consist of approximately 8–10 open-ended questions covering four main areas: (1) perceived attractiveness and acceptability of the program, (2) usability and ease of engagement, (3) motivational and challenging factors for sustaining self-management behaviors, and (4) suggestions for further development of AI-HEALS. These interviews aim to provide deeper insights into the factors motivating participation and behavioral change. Participants will be invited to engage in approximately 30-min telephone or face-to-face in-depth interviews. Selection of participants will consider sociodemographic variables such as gender, age, location, education level, and pain intensity. Recruitment will continue until thematic saturation is achieved. Audio recordings of interviews will be transcribed verbatim, anonymized, and analyzed, with data coding and management conducted in NVivo (Version 12, QSR International, Doncaster, Australia). Both qualitative and quantitative data will be integrated to better interpret the results across multiple phases of the trial.

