### Sample size

2.4

G-Power 3.1.9.4 was used to calculate the sample size. The effect size was 0.68 (33), efficacy was 0.80, alpha was set at 0.05, and one-tailed tests were performed based on previous studies. The calculated required sample size was determined to be at least 58 (29 participants per group). We estimated an attrition rate of 20%, so a total sample of at least 74 participants (37 per group) was required.

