#### Primary outcomes

2.10.1

Changes in pain intensity from baseline to discharge, at the end of the intervention, and during follow-up periods at 3, 6, and 9 months post-intervention.

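### The tests named for comparing the arms are unadjusted and baseline VAS is not named as a covariate, although it is collected and would add power in this small trial

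*Protocol article*

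**What the plan says.** Section 2.10.1 defines the primary outcome as "Changes in pain intensity from baseline" to discharge, to the end of the three-month intervention, and to three later follow-up visits. Table 1 schedules VAS at baseline and at each of these five visits.

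Section 2.13 does three things that bear on the comparison of arms:

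- Continuous variables are presented as mean and SD or as median and quartiles, "depending on the normality of the distribution", which a Kolmogorov–Smirnov test assesses.
- The next sentence offers Student's t-test as one example of a suitable method and goes on: "one-way ANOVA, or non-parametric tests, will be used for group comparisons". No covariate is mentioned.
- A later sentence states that "generalized linear mixed models will be used to assess the impact of AI-HEALS interventions on behavior change and NSLBP management over time". It does not say whether VAS is a response in that model, whether the model is primary, or how baseline enters.

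Section 2.4 sizes the trial at 29 evaluable patients per arm and 37 after attrition.

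**The concern.** Every test named for group comparisons is unadjusted. Applied to change from baseline, such a test fixes the coefficient of baseline at one instead of estimating it. This has two consequences when follow-up VAS is imperfectly correlated with baseline. First, the change score carries more residual variance than an analysis with baseline as a covariate. Second, a chance difference between arms at baseline passes partly into the estimated effect. Both matter more in a trial of this size than in a large one.

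The information needed to avoid both is collected from every participant. At stake is precision on the primary outcome that could be had without recruiting anyone or measuring anything new.

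**Working it through.** **Inputs from the protocol.** Section 2.4: effect size 0.68, power 0.80, alpha 0.05, "one-tailed tests were performed based on previous studies", 29 per arm evaluable, 20% attrition, 37 per arm in total. Section 2.13: all tests two-sided at 0.05.

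**Assumptions, not in the protocol.** Baseline-to-follow-up correlation r = 0.3, 0.5 or 0.7; the same VAS standard deviation σ at baseline and follow-up. Section 2.4 does not say whether 0.68 is in units of the final-score SD or the change-score SD, so both are shown.

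**Step 1: the plan's own figure.** Power is taken from the noncentral t distribution with noncentrality d√(n/2) and 2n − 2 degrees of freedom. At d = 0.68 and one-sided 0.05, 28 per arm give 0.807 and 29 give 0.819. For a rank test with efficiency 3/π, d becomes 0.68 × √(3/π) = 0.66 and 29 per arm are needed. Attrition: 29/0.8 = 36.25, rounded up to 37 per arm, 74 in total. The stated size is thus reproduced (within one patient per arm for the t-test) by an unadjusted one-sided comparison.

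**Step 2: the two-sided test.** With 29 per arm the noncentrality is 0.68 × √14.5 = 2.59 and power is 0.72.

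**Step 3: residual variance, in units of σ².**

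- Final score: 1
- Change score: 2(1 − r)
- Adjusted for baseline: 1 − r²

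Adjusted over change is (1 − r²)/(2(1 − r)) = (1 + r)/2, that is 0.65, 0.75 and 0.85 at r = 0.3, 0.5 and 0.7. Adjusted over final is 0.91, 0.75 and 0.51.

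**Step 4: two-sided power at 29 per arm.** If 0.68 is on the final-score SD, the effective d is 0.68/√(2(1 − r)) for the change score and 0.68/√(1 − r²) for the adjusted analysis. If 0.68 is on the change-score SD, the change-score d stays 0.68 and the adjusted d is 0.68/√((1 + r)/2). The adjusted analysis loses one degree of freedom.

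| Scale of 0.68 | r | Change score: d, power | Adjusted: d, power |
|---|---|---|---|
| Final-score SD | 0.3 | 0.57, 0.58 | 0.71, 0.76 |
| Final-score SD | 0.5 | 0.68, 0.72 | 0.79, 0.84 |
| Final-score SD | 0.7 | 0.88, 0.91 | 0.95, 0.95 |
| Change-score SD | 0.3 | 0.68, 0.72 | 0.84, 0.88 |
| Change-score SD | 0.5 | 0.68, 0.72 | 0.79, 0.84 |
| Change-score SD | 0.7 | 0.68, 0.72 | 0.74, 0.79 |

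**Step 5: chance imbalance.** The standard error of the baseline difference between arms is √(2/n) SD: √(2/29) = 0.26 and √(2/37) = 0.23. A difference of 0.25 SD is therefore ordinary. Given a baseline difference of Δ SD, the change-score estimate is off by (1 − r)Δ. With Δ = 0.25 this is 0.175, 0.125 and 0.075 SD at r = 0.3, 0.5 and 0.7. Against 0.68 on the final-score SD, that is 26%, 18% and 11% of the planned effect. Averaged over randomisations the error is zero; in the one trial that is run it is not. Covariate adjustment removes it.

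**The case against.** The strongest reply is that the article fixes less than a critic would like to read into it, and most of that reply stands.

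- **The tests are examples.** They are introduced as illustrations, in the paragraph on how variables are presented, and are not labelled the primary analysis of VAS. This stands. They are nevertheless the only methods named for group comparisons, and all are unadjusted.
- **The mixed model may adjust for baseline.** A reader might infer that no planned analysis uses baseline VAS as a covariate. The protocol does not support that: the model's covariates are unstated, and a covariate list may sit in an analysis plan that is not shown. It can be said only that baseline VAS is not named.
- **Baseline is not ignored.** A reader might infer that it is. It enters by subtraction, because the outcome is change. At r = 0.7 the change score already has 0.91 power on the final-score scale, and adjustment adds only 0.04.
- **A normality test does not expressly choose the test.** A reader might infer this because parametric and rank methods follow in the next sentence with no other rule for selecting between them. The text ties the Kolmogorov–Smirnov test only to how data are summarised.
- **The drop to 0.72 has another cause.** It comes from the conflict between the one-tailed sample size and the two-sided tests, which is a separate point. Adjustment may offset it but does not explain it.
- **Stratification.** The randomisation section mentions none, which does not establish that there is none.

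**Conclusion.** The point holds as a worthwhile improvement, not as an error that invalidates the trial. For an outcome defined as change from baseline, the methods named are less efficient than one that needs only data already collected.

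In all six scenarios adjustment beats the raw change score, by between 0.04 and 0.18 in power. It does not always bring power back to 0.80: it stops at 0.76 when r = 0.3 on the final-score scale, and at 0.79 when r = 0.7 on the change-score scale. The ordering of the two methods follows from the variance formulas under equal SDs. The size of the gain rests on r and on the scale of 0.68, neither of which the protocol gives, so no single figure should be quoted as the loss.

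**What to change.** State in section 2.13 that VAS is compared between arms with a model that includes baseline VAS as a covariate. This can be an ANCOVA, or the mixed model already planned with VAS as response and baseline VAS among its covariates. State that this model is used whatever a normality test shows. Keep the unadjusted t-test or a rank test as a named sensitivity analysis. The covariance structure and the choice of primary time point can be left to the sponsor.

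The cost is a sentence or two. No extra patients, visits or measurements are needed. SPSS and Stata, both listed, fit these models, and they can be run in each of the 20 imputed datasets already planned. The trial is expected to run to December 2026; the wording should be fixed before anyone sees outcomes by arm.

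### Subgroup analyses by levels of two baseline scores should be judged by treatment-by-score interactions with the scores kept continuous, not by splitting a trial sized only for the overall effect

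*Protocol article*

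**What the plan says.** Section 2.13 (Statistical analysis) states that subgroup analyses will be based on patients' "levels of family communication and eHealth literacy to refine and contextualize the findings". The preceding sentence plans generalized linear mixed models for the longitudinal analyses. The section also says: "All statistical tests will be two-sided, with a significance level set at 0.05". It gives no number of levels, cut-point or method for comparing levels.

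The two factors are the FCS-SF (four items) and the eHEALS (five items). Section 2.12 describes both as total scores where higher means more, without bands or thresholds. Table 1 schedules both at baseline only.

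Section 2.4 (Sample size) covers only the overall comparison: "The effect size was 0.68 (33), efficacy was 0.80, alpha was set at 0.05, and one-tailed tests were performed based on previous studies". After attrition, "a total sample of at least 74 participants (37 per group) was required".

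**The concern.** Analysing by levels of a numeric score that has no bands means, on the plain reading, cutting the score and forming groups. The trial has just enough patients for one overall comparison, so each group has low power. If groups are then tested one by one, a significant result in one and a non-significant result in the other is common even when the programme works equally well in both.

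For a programme delivered through WeChat, such a pattern is easily read as benefit only in patients with high eHealth literacy. That could wrongly narrow who is offered it. The stated purpose of the subgroup results is to refine the findings, so they will be interpreted. Grouping can also discard information about how the effect varies with the score, even where levels are compared properly.

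**Working it through.** **Inputs.** Standardised effect 0.68, power 0.80, one-sided 0.05, 29 per arm evaluable, 20% attrition, 37 per arm enrolled (section 2.4); 1:1 allocation (section 2.2); two-sided 0.05 for all tests (section 2.13). Assumed, because the article does not state them: a two-level split, separate t-tests in each level at a single time point, and the same true effect in both levels.

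**The plan's own figure.** At 0.68, one-sided 0.05 and power 0.80, the exact t-test needs 28 per arm. The Wilcoxon-Mann-Whitney version (relative efficiency 3/π) needs 29, the article's figure. Attrition: 29/0.8 = 36.25, rounded up to 37 per arm, 74 in total. The sample size reproduces, and it contains nothing for subgroups.

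**Separate tests in two halves.** Let p be the power of a two-sided 0.05 t-test within a half (noncentral t). With equal halves, P(exactly one significant) = 2p(1 − p).

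| Patients | Per arm per half | p at 0.68 | Exactly one significant | Simulated (20,000 trials) |
|---|---|---|---|---|
| 58 | 58/4 = 14.5 | 0.423 | 2 × 0.423 × 0.577 = 48.8% | 48.6% |
| 74 | 74/4 = 18.5 | 0.520 | 2 × 0.520 × 0.480 = 49.9% | 49.7% |

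**Dependence on the true effect (74 patients).**

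| True effect in both halves | p | Exactly one significant |
|---|---|---|
| 0 | 0.050 | 9.5% |
| 0.3 | 0.144 | 25% |
| 0.5 | 0.316 | 43% |
| 0.68 | 0.520 | 50% |
| 0.8 | 0.658 | 45% |
| 1.0 | 0.841 | 27% |

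**Other splits at 0.68.** Splits from 40/60 to 25/75 give 50-59%. Tertiles give mixed results 62-70% of the time. With median splits on two independent scores, at least one score is discordant in 66-67% of simulated trials.

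**Interaction with the continuous score, uniform true effect.** Simulated false-flag rate per score: 5.1% (74 patients) and 4.8% (58). For either of two independent scores: 1 − 0.95² = 9.75%; simulated 9.9% and 9.4%.

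**Interaction power.** Take a true difference of 0.68 SD between the mean effects in the lower and upper score halves, a normally distributed score and an effect linear in the score (normal approximation).

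- Median-split interaction: SE = √(16/N), which is 0.465 at 74 and 0.525 at 58. Then 0.68/SE = 1.46 and 1.29, so power is 31% and 25%.
- Continuous interaction: slope = 0.68/(2√(2/π)) = 0.426 per SD of score; SE = 2/√N, which is 0.232 and 0.263. The ratios are 1.83 and 1.62, so power is 45% and 37%.
- Simulation with t-tests gives somewhat lower values: about 41% against 29% at 74, and 32% against 23% at 58.

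**If the effect is not linear.** Suppose it changes in a single step exactly at the median. The expected linear slope is then 0.68 × 1/√(2π) = 0.271. The ratios are 0.271/0.232 = 1.17 and 0.271/0.263 = 1.03, so the continuous test has about 21% and 18% power, against 31% and 25% for the split. The gain therefore depends on a roughly steady trend with the score.

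**The case against.** A reader might infer that the plan will produce a false subgroup difference half the time. The article does not support that. It names no median split, no within-level tests and no comparison of their significance. Section 2.12 uses the word level for a plain numeric score, the subgroup sentence directly follows the mixed-model sentence, and grouped levels judged by an interaction test would have about 5% error. Cut-points and interaction terms are also details that an article commonly leaves to an analysis plan, so their absence is not a finding. All of this stands, and so the half-the-time figure is conditional. It also lies close to the maximum of 2p(1 − p), which is 50%, and falls away for smaller or larger true effects.

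A second objection is that the calculation is not the planned analysis. It uses one time point, whereas the plan has repeated measures, intention-to-treat and multiple imputation. This also stands. The figures for 74 patients answer the sample-size part; the repeated-measures model would shift the numbers.

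A reader might also infer that the interaction removes the problem at no cost. It does not: about 5% false flags per score remain, power is low, and linearity is assumed.

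What survives is the choice that the article does state, namely analysis by levels of two unbanded numeric scores. Even on the kindest reading, with an interaction test on groups, that choice gives up power under a steady trend, although the data and model for the better method are already in the plan.

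**Conclusion.** The point holds as an improvement to a stated analysis choice, not as an error in a stated figure. If the scores are halved and each half is tested separately, discordant significance occurs in about 49-50% of trials per score at a uniform effect of 0.68, and in about 10-50% over true effects from 0 to 1.0 at 74 patients. If levels are instead judged by interaction, error is controlled but grouping lowers power from roughly 41-45% to 29-31% at 74 patients, and from 32-37% to 23-25% at 58. These power figures assume an effect that is linear in the score. Neither method can establish that the effect is uniform in a trial of this size, which is a reason to label the results exploratory.

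**What to change.** In section 2.13, state that effect modification will be judged by treatment-by-FCS-SF and treatment-by-eHEALS interactions, scores kept continuous, in the planned mixed model. Include the main effect of each score, and score-by-treatment-by-time terms where the model needs them. Report each interaction with its 95% CI as exploratory. Show effects at a low and a high score for description only, with no claims of significance within levels. Say explicitly that a null interaction will not be read as proof of a uniform effect.

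While editing, reconcile the FCS-SF range in section 2.12: it is given as 5 to 20, but four items scored 1 to 5 give 4 to 20.

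The cost is a few sentences and a few model terms, with no added patients, visits or instruments. The downsides are the linearity assumption and the limited power. According to the Trial status section the study runs to December 2026, so the text can be settled before the analysis.
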